### Randomization and Blinding

Participants will be randomized in a 1:1 ratio using a secure, web-based randomization system embedded within the REDCap trial database. Randomization will be stratified by age, country, and transplant type (kidney alone or SPK), with the use of random permuted blocks to ensure balanced allocation across treatment groups within each center.

Given the nature of the intervention, complete blinding is not feasible. Therefore, clinicians and participants will be unblinded to the treatment allocation. However, measures are in place to preserve blinding among other key stakeholders. The BEAT-BK Global Steering Committee (GSC), site investigators, and the Trial Management Committee will remain blinded to individual treatment allocations and any aggregate data that could compromise unblinding of study outcomes. Although the statistical analysis team will be unblinded during interim analyses, a designated trial statistician will remain blinded throughout to support final primary analysis. All enrolled participants will be followed for a total of 48 wk after randomization.

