Reductions in immunosuppression will be defined as minimal, moderate, or large, depending on the degree of immunosuppression reduction required at 12 wk postrandomization (Table 3). The largest reduction in any single immunosuppressive medication (excluding steroid therapy) will be considered for outcome classification. Reductions in antimetabolites will be categorized according to the percentage reduction relative to initial dosing. Reductions in tacrolimus, ciclosporin, and mammalian target of rapamycin (mTOR) inhibitors will be categorized as the reduction in trough target levels at 12 wk relative to initial target trough levels. For patients receiving tacrolimus, ciclosporin, and mTOR inhibitors, their treating clinicians will be asked to specify target levels at randomization and again at 12 wk. Reductions in steroid dosing will not be considered part of the ranked outcome. Substantial variation exists between centers in the use of steroids after transplantation, with some centers adopting steroid-free programs. Therefore, in this cohort, reductions in steroid doses may be unrelated to BKPyV infections.

**TABLE 3. T3:** Classification of immunosuppression reduction by degree of reduction

Immunosuppression medication	Degree of reduction^*a*^	Large	Moderate	Minimal
Antimetabolite	Dose reduction from baseline (%)	≥75%	>25–<75%	≤25%
Ciclosporin (C0 or C2)	Target-level reduction from baseline (%)	≥75%	>25–<75%	≤25%
mTOR-I (trough)				
Tacrolimus (trough, ng/mL)	Baseline trough	Final target trough	Final target trough	Final target trough
	≥8	≤3.9 (or cessation)	4–6.9	≥7
	6–8	≤3.9 (or cessation)	4–5.9	≥6
	4–6	≤2.9 (or cessation)	3–3.9	≥4
	<4	Cessation	≤2.9 (>0)	≥3

^*a*^ The largest reduction in any single immunosuppressive medication (excluding steroid therapy) will be considered for outcome classification.

mTOR, mammalian target of rapamycin.

In addition to dose reductions, conversion from a more potent to a less potent immunosuppressive agent in direct response to BKPyV infection will be classified as a “large” reduction. Conversions performed for other indications, such as drug intolerance, adverse effects, or malignancy, should not be considered a “large” reduction.

Conversions that qualify as “large” immunosuppressive reductions include:

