### Trial Oversight

The study will be conducted and coordinated by the Australasian Kidney Trials Network. The study will be conducted according to Good Clinical Practice guidelines and the reporting of results will follow the Consolidated Standards of Reporting Trials guidelines.^22^

The Australasian Kidney Trials Network will establish and manage key oversight bodies, including an independent Data and Safety Monitoring Board (DSMB), an Endpoint Verification Committee, and a Consumer Advisory Board. The DSMB, comprising independent experts in clinical trials, nephrology, infectious diseases, and biostatistics, will monitor participant safety and trial progress, and may recommend early termination because of efficacy or safety concerns. While the DSMB will report to the GSC Chair, all final decisions on trial modifications or early stopping will rest with the GSC.

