### Safety

Participant safety will be closely monitored throughout the trial, with all AEs, adverse drug reactions, serious AEs, suspected unexpected serious adverse reactions, and AEs of special interest reported by site staff and reviewed by the DSMB. Investigators will assess the relationship between any adverse event and IVIg administration using a standardized scale (none, unlikely, possible, or probable). All safety data will be reviewed by the DSMB (**Table S2, SDC,**
https://links.lww.com/TXD/A839), which is responsible for evaluating participant safety and determining whether any trial modifications or early stopping are warranted.

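### The plan lists site investigators as blinded, which this open-label design cannot deliver, and unblinded clinicians determine categories 1–3 of the primary outcome, so less tapering under IVIg could read as benefit

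*Protocol article*

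**What the plan says.** Protocol article, Randomization and Blinding: complete blinding is said not to be feasible, and "clinicians and participants will be unblinded to the treatment allocation". The paragraph then says that "The BEAT-BK Global Steering Committee (GSC), site investigators, and the Trial Management Committee will remain blinded to individual treatment allocations", and extends this to aggregate data that could compromise blinding. Under Safety, "Investigators will assess the relationship between any adverse event and IVIg administration using a standardized scale", running from none to probable.

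Under Primary Outcome, with no category 4 or 5 event, a participant is placed in category 1, 2 or 3 by the degree of immunosuppression reduction, less being better. Tacrolimus, ciclosporin and mTOR inhibitors "will be categorized as the reduction in trough target levels at 12 wk relative to initial target trough levels"; for these drugs "their treating clinicians will be asked to specify target levels at randomization and again at 12 wk". For the other main class, "Reductions in antimetabolites will be categorized according to the percentage reduction relative to initial dosing". The largest reduction in any one drug decides, steroids excluded. A conversion to a less potent agent counts as large only when made in direct response to BKPyV. The Intervention section gives a reduction algorithm but lets clinicians depart from it on local standards and clinical judgment.

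Trial Oversight names "an independent Data and Safety Monitoring Board (DSMB), an Endpoint Verification Committee, and a Consumer Advisory Board". The article does not describe the verification committee's task or masking.

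**The concern.** There are two linked problems. First, the blinding statement is wrong as written. A reader would take it that someone at site level assesses participants without knowing the arm, and nothing else in the article makes that possible.

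Second, the three best categories of the primary outcome measure what an unblinded clinician chose to do and to report. A clinician who expects IVIg to work may taper less, or may state a higher week-12 target. Either moves IVIg participants from category 3 to 2, or from 2 to 1, and the common odds ratio counts the move as efficacy. Stopping for superiority depends on the posterior probability that this odds ratio is below 0.9, so the same movement feeds the stopping decision.

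**Working it through.** **1. The blinding text.** The sentence names individual allocations as well as aggregate data, so it cannot be read as covering aggregate data only. Only one arm receives infusions, and investigators rate events against those infusions. The passages agree only if site investigators never treat participants or rate events, which the article does not say.

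**2. Routes into categories 1–3.** Three inputs are in unblinded hands: the stated target, the antimetabolite dose, and the stated reason for a conversion. Categories can turn on small differences. Strategy 2 in Table 1 gives a tacrolimus target range of 3–5 ng/mL, which straddles cut-offs in Table 3. From baseline troughs of 6 upward, a final target of 3.9 is large and 4 is moderate; from baseline 4–6, 3.9 is moderate and 4 is minimal.

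**3. Size, with no true effect.** From Statistical Analyses: looks at 100, 160, 220 and 280 participants; N(0,1) prior on the log odds ratio; superiority if P(OR<0.9) > 0.95; futility if < 0.10. From Randomization and Blinding: 1:1 allocation. The article gives no category rates, so these are assumed, with 35%, 50% or 65% of participants in categories 4–5. A share s of category 3 moves to 2, and of category 2 to 1, in the IVIg arm only:

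p1' = p1 + s·p2; p2' = p2 − s·p2 + s·p3; p3' = p3 − s·p3; p4 and p5 unchanged.

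Example: control 15/25/25/25/10% and s = 0.4 give IVIg 25/25/15/25/10%. The cumulative odds ratios for a worse outcome are:
- above category 1: (75/25)/(85/15) = 0.53
- above category 2: (50/50)/(60/40) = 0.67
- above category 3: 1.00
- above category 4: 1.00

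The fitted common odds ratio is 0.752, although rejection, viraemia, eGFR decline, graft loss and death do not differ.

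Simulation: 6000 trials per row, normal approximation to the posterior, no covariates or dropout, Monte Carlo error about 0.3–0.6 points.

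| Control mix, categories 1–5 (%) | OR, s=0.2 | OR, s=0.4 | False superiority, s=0 / 0.2 / 0.4 |
|---|---|---|---|
| 15/25/25/25/10 | 0.867 | 0.752 | 4.2 / 11.9 / 28.0% |
| 10/20/20/35/15 | 0.914 | 0.836 | 4.1 / 8.3 / 15.7% |
| 7/14/14/45/20 | 0.955 | 0.912 | 4.3 / 6.2 / 8.3% |
| 21.7 each in 1–3/25/10 | 0.888 | 0.788 | 4.4 / 10.8 / 22.9% |
| 16.7 each in 1–3/35/15 | 0.931 | 0.867 | 4.2 / 6.6 / 12.1% |
| 11.7 each in 1–3/45/20 | 0.964 | 0.930 | 4.1 / 5.1 / 7.1% |

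A separate set of runs with the same 35/50/65% shares gave 6–8% at s = 0.2 and 8–24% at s = 0.4. The result depends on the assumed mix.

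**4. Leakage into category 4.** Suppose a fraction of the under-tapered participants stays above 1000 copies/mL. In the example, 20 points move in all (10 from category 3, 10 from category 2). With 25% leakage, 5 of them go to category 4, giving 22.5/22.5/15/30/10%. Over the six mixes at s = 0.4:
- 25% leakage: OR 0.909–1.000, false superiority about 4–9%
- 50% leakage: OR 1.07–1.11, false superiority about 1–2%, so the bias reverses

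**5. Supportive fit with categories 1–3 collapsed.** At s = 0.4 without leakage, 98–100% of false superiority claims had a collapsed odds ratio below 1. Direction therefore does not discriminate. The collapsed posterior probability is more informative: P(OR<0.9) exceeded 0.95 in 8–46% of those false claims, against 48–77% of the false claims that arose with no shift.

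**The case against.** The strongest reply is that the bias runs through treating clinicians, whom the article openly declares unblinded. Correcting the phrase about site investigators leaves that route untouched, and what remains is a general limitation of open-label trials. This stands: a reader might infer that the wrong blinding statement causes the bias, and it does not. They are two problems with two remedies.

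A reader might also infer that stated targets alone set categories 1–3. They do not. Under Strategy 1 in Table 1 the antimetabolite is cut by at least 50% first, which is already at least moderate in Table 3, so a higher stated calcineurin-inhibitor target cannot bring such a participant to category 1. But antimetabolite dose is also set by unblinded clinicians, and departure from the algorithm is allowed.

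The endpoint was built for this trade-off: a viral load above 1000 copies/mL gives category 4. That protection is real but partial, since it catches under-tapering only when viraemia or rejection is present at week 12. Table 4 also reports viral load, eGFR decline, rejection, graft loss and death separately, which helps interpretation but does not alter the primary decision.

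Finally, it is tempting to say that baseline targets are recorded after allocation is known, or that no masked classification exists. The article does not show either. Field order and a committee charter belong to the full protocol and may already be settled. Less tapering may also be a true effect of IVIg through faster viral control, and the endpoint cannot separate the two.

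**Conclusion.** The concern holds in limited form. The statement that site investigators are blinded to individual allocations conflicts with its own paragraph and with the Safety section, and needs correcting whatever one thinks of the bias. Categories 1–3 depend on decisions and statements of unblinded clinicians, so a difference in tapering alone can take the common odds ratio below 0.9.

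The size rests on assumed category mixes and assumed shifts; the documents support no particular value for either. Roughly 5–12% and 7–28% false superiority (20% and 40% shift, against about 4%) are upper cases with no leakage into category 4. The effect is small when most participants are in categories 4–5, and it vanishes or reverses with moderate leakage. The article's statement that type 1 error is controlled is not shown to be false: its simulations are in a supplement not seen here, and the shift modelled is a bias in the data, not a flaw in the stopping rule.

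**What to change.** 1. Remove site investigators from the blinded list, or restrict the statement to aggregate data by arm.
2. Make baseline target levels a required, locked field before the randomization system releases the allocation. If the full protocol or database already does this, say so.
3. Prespecify a supportive proportional-odds fit with categories 1–3 collapsed. Report its odds ratio, credible interval and P(OR<0.9) beside the primary result, and state that superiority driven only by categories 1–3 may reflect open-label prescribing. Do not use agreement in direction as the test of robustness.
4. Where the Endpoint Verification Committee classifies outcomes, have it do so without arm information, and acknowledge that this can correct classification but cannot remove differences in prescribing.

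The cost is a wording change, a database field order and one extra model fit, plus masking of committee material where the committee classifies outcomes. No clinical rule changes.

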### Primary Outcome

The primary outcome is a composite, ordinal outcome assessed at 12 wk (with an acceptable window of 11–13 wk) after randomization (Table 2; Figure 1). Each participant will be assigned to a category on a 5-point ordinal scale, with higher scores indicating worse outcomes:

**TABLE 2. T2:** Primary composite ordinal outcome at 12 wk postrandomization

Primary objective	Outcome measure(s)	Time-point(s)
To compare the efficacy of immunosuppression reduction/ modification strategies, with and without IVIg, on BKPyV infection in kidney and simultaneous kidney-pancreas transplantation recipients	A composite, ordinal outcome defined as: 5: All-cause death or allograft loss (kidney and/or pancreas) or eGFR decline ≥10 mL/min/1.73 m^2^ using the CKD-EPI formula^*a*^ for adults and the Schwartz formula^*a*^ for children 4: Acute rejection (kidney and/or pancreas) or BKV load >1000 copies/mL 3: Large reduction in immunosuppression relative to baseline 2: Moderate reduction in immunosuppression relative to baseline 1: Small to no reduction in immunosuppression relative to baseline Participants will be assigned a category between 1 (best) and 5 (worst).	Week 12

^*a*^ Pancreas graft function loss is defined as kidney-pancreas transplantion recipients’ insulin use is ≥0.5 units/kg/d for 90 consecutive days, or when the recipient’s pancreas graft is removed, and/ or re-registered for a pancreas transplantation.

BKPyV, BK polyomavirus; CKD-EPI, Chronic Kidney Disease Epidemiology Collaboration; eGFR, estimated glomerular filtration rate; IVIg, intravenous immunoglobulin; NB, all timepoints in the above table commence from the date of randomization.

**FIGURE 1. F1:**
[figure not shown]
Primary composite ordinal outcome assessed at 12 wk.

Category 5: All-cause death *or* allograft loss (kidney and/or pancreas) *or* an estimated glomerular filtration rate (eGFR) decline of ≥10mL/min/1.73 m2 using the race-free creatinine-based Chronic Kidney Disease Epidemiology Collaboration equation formula for adults^12^ and the Chronic Kidney Disease in Children 2012 for children.^13^

Category 4: Biopsy-proven acute rejection (T cell–mediated, antibody-mediated, mixed, and borderline rejection in the kidney and/or pancreas) *or* has a BKPyV DNAemia exceeding 1000 copies/mL.

Category 3: Required a “large” reduction in immunosuppression relative to *baseline.

Category 2: Required a “moderate” reduction in immunosuppression relative to baseline.

Category 1: Required a “small” to no reduction in immunosuppression relative to baseline.

**Baseline is defined as “at the time of randomization.”*

This composite ordinal outcome was chosen because BKPyV infection has multifaceted effects on both the allograft and the transplant recipient.^14^ BKPyV viral load is a reliable marker of infection, and at a threshold of 5 × 10^3^ copies/mL, has a positive predictive value of approximately 50% for BKPyVAN in kidney and SPK transplant recipients.^15,16^ Kidney allograft function, as measured by changes in eGFR, is known to predict longer-term allograft loss.^17^ Furthermore, a minimal requirement for immunosuppression reduction during BKPyV management likely reflects effective viral control and is associated with more favorable long-term outcomes.

Despite the utility of these measures, relying on any single outcome would be insufficient to capture the complex trade-offs involved in managing BKPyV.^14^ For instance, an aggressive reduction in immunosuppression may lead to a rapid decline in viral load, but at the cost of increased risk of acute rejection, graft dysfunction or even graft loss. Conversely, overly conservative management may preserve allograft function in the short term while allowing progressive viral injury to develop. To address these competing risks, the ordinal composite outcome has been adopted. Participants will be categorized based on a combination of death, graft loss, rejection, graft dysfunction, viral load, and the degree of immunosuppression reduction required, providing a more holistic assessment of treatment response.

Reductions in immunosuppression will be defined as minimal, moderate, or large, depending on the degree of immunosuppression reduction required at 12 wk postrandomization (Table 3). The largest reduction in any single immunosuppressive medication (excluding steroid therapy) will be considered for outcome classification. Reductions in antimetabolites will be categorized according to the percentage reduction relative to initial dosing. Reductions in tacrolimus, ciclosporin, and mammalian target of rapamycin (mTOR) inhibitors will be categorized as the reduction in trough target levels at 12 wk relative to initial target trough levels. For patients receiving tacrolimus, ciclosporin, and mTOR inhibitors, their treating clinicians will be asked to specify target levels at randomization and again at 12 wk. Reductions in steroid dosing will not be considered part of the ranked outcome. Substantial variation exists between centers in the use of steroids after transplantation, with some centers adopting steroid-free programs. Therefore, in this cohort, reductions in steroid doses may be unrelated to BKPyV infections.

**TABLE 3. T3:** Classification of immunosuppression reduction by degree of reduction

Immunosuppression medication	Degree of reduction^*a*^	Large	Moderate	Minimal
Antimetabolite	Dose reduction from baseline (%)	≥75%	>25–<75%	≤25%
Ciclosporin (C0 or C2)	Target-level reduction from baseline (%)	≥75%	>25–<75%	≤25%
mTOR-I (trough)				
Tacrolimus (trough, ng/mL)	Baseline trough	Final target trough	Final target trough	Final target trough
	≥8	≤3.9 (or cessation)	4–6.9	≥7
	6–8	≤3.9 (or cessation)	4–5.9	≥6
	4–6	≤2.9 (or cessation)	3–3.9	≥4
	<4	Cessation	≤2.9 (>0)	≥3

^*a*^ The largest reduction in any single immunosuppressive medication (excluding steroid therapy) will be considered for outcome classification.

mTOR, mammalian target of rapamycin.

In addition to dose reductions, conversion from a more potent to a less potent immunosuppressive agent in direct response to BKPyV infection will be classified as a “large” reduction. Conversions performed for other indications, such as drug intolerance, adverse effects, or malignancy, should not be considered a “large” reduction.

Conversions that qualify as “large” immunosuppressive reductions include:

Tacrolimus to ciclosporin;Tacrolimus to an mTOR inhibitor;Ciclosporin to an mTOR inhibitor;Conversion to from a CNI to azathioprine alone;Mycophenolate mofetil/mycophenolic acid to azathioprine;Mycophenolate mofetil/mycophenolic acid to an mTOR inhibitor;Azathioprine to an mTOR inhibitor.

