### Intervention

Participants will be randomized to 1 of 2 treatment arms: standard immunosuppression reduction alone or immunosuppression reduction in combination with IVIg. The total intended IVIg dose over the 8-wk intervention period will be 2 g/kg, with a tolerance range of 1.8–2.2 g/kg. The recommended dosing schedule is 250 mg/kg weekly for 8 wk, with a 2-wk administration window for flexibility. The first dose of IVIg must be given within 14 d of randomization. Because of potential supply and logistical constraints, the protocol permits IVIg doses to be combined, allowing for up to 2 doses (up to 500 mg/kg) to be administered during a single session.

In both arms, immunosuppression reduction is implemented per current standard of care following a standardized algorithm adapted from the 2024 Transplantation Society guidelines (Table 1).^11^ This typically involves a stepwise reduction in calcineurin inhibitors (CNIs) and antiproliferative agents, or conversion to less potent agents. The protocol provides flexibility for clinicians to alter immunosuppressive therapy according to local standards and clinical judgment. The treatment goal is to achieve a BK viral load <1000 copies/mL, where feasible.

**TABLE 1. T1:** Recommended approach to immunosuppression reduction (adapted from The Second International Consensus Guidelines on the Management of BK Polyomavirus in Kidney Transplantation, 2024^11^)

Strategy 1: Antimetabolite is reduced first
Reduction of the dose of antimetabolite by at least 50%
We suggest further immunosuppression reduction if BKPyV DNAemia does not decrease by 10-fold at 4 wk or does not clear below lower limit of detection as follows:
Discontinuation of the antimetabolite and tapering of corticosteroid dose to 5–10 mg/d of prednisone or equivalent, if applicable
We suggest adding prednisone (or equivalent) 5–10 mg/d for patients who are not on corticosteroids to avoid CNI monotherapy
If further decrease in immunosuppression is necessary, we suggest a stepwise reduction of the CNI dose (tacrolimus trough target 5 ng/mL; cyclosporine trough target 100 ng/mL)
Strategy 2: CNI is reduced first
Reduction of the dose of CNI by 25%–50% in 1 or 2 steps to target trough concentrations of tacrolimus of 3–5 ng/mL and cyclosporine trough concentrations of 75–125 ng/mL)
We suggest further immunosuppression reduction if BKPyV DNAemia does not decrease by 10-fold at 4 wk or does not clear below lower limit of detection as follows:

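### Table 3's tacrolimus rows give two classes for a baseline target of exactly 8 or 6, and score an unchanged or raised target below 3 as a Moderate reduction

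*Protocol article*

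**What the plan says.** Table 2 of the Protocol article defines category 1 of the primary outcome as "Small to no reduction in immunosuppression relative to baseline" and category 2 as "Moderate reduction in immunosuppression relative to baseline"; category 3 is a large reduction. Categories 4 and 5 are reached through rejection, viral load, eGFR decline, graft loss or death.

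The text introducing Table 3 sets the rule for grading a reduction. Reductions in tacrolimus, ciclosporin and mTOR inhibitors "will be categorized as the reduction in trough target levels at 12 wk relative to initial target trough levels". On the source of those values, "their treating clinicians will be asked to specify target levels at randomization and again at 12 wk". Across drugs, "The largest reduction in any single immunosuppressive medication (excluding steroid therapy) will be considered for outcome classification".

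Table 3 then gives tacrolimus four baseline rows (ng/mL), each with its own cut-offs for the final target:

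| Baseline | Large | Moderate | Minimal |
|---|---|---|---|
| ≥8 | ≤3.9 or cessation | 4–6.9 | ≥7 |
| 6–8 | ≤3.9 or cessation | 4–5.9 | ≥6 |
| 4–6 | ≤2.9 or cessation | 3–3.9 | ≥4 |
| <4 | cessation | ≤2.9 (above 0) | ≥3 |

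No sentence in the article says which row owns a baseline of 8 or of 6, or how an unchanged target below 3 is to be scored.

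**The concern.** A primary endpoint has to map each participant to one category. Here two adjacent pairs of rows share an endpoint and carry different cut-offs, so the same pair of recorded targets can yield two classes. Separately, the <4 row looks only at the final value and ignores where the participant started, so a target that has not moved, or has gone up, can be scored as a reduction. That conflicts with the definition of category 1 and with the text's own rule that the class is a change from the initial target.

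The 12-week outcome feeds the proportional odds model that drives the interim decisions, after 100 participants reach the endpoint and every 60 thereafter. The same scale is reused for the week-48 composite and for the analysis based on the regimen at first qualifying viral load.

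**Working it through.** **Inputs.** The four tacrolimus rows as printed in Table 3; the text's rule that targets are compared; the largest-reduction rule; the category definitions in Table 2. The plan states no figure to reproduce, since this is a classification table.

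**Method.** The rows were coded as printed. Every baseline target from 0.1 to 15.0 was paired with every final target from 0 (cessation) to 15.0, in steps of 0.1 ng/mL. Two things were counted: pairs that match two rows with different classes, and pairs where the final target is not below the baseline yet the class is not Minimal.

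**Result 1: shared endpoints.**

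| Baseline | Final | Upper row gives | Lower row gives | Outcome category | Pairs |
|---|---|---|---|---|---|
| 8 | 6.0–6.9 | Moderate (≥8) | Minimal (6–8) | 2 or 1 | 10 |
| 6 | 4.0–5.9 | Moderate (6–8) | Minimal (4–6) | 2 or 1 | 20 |
| 6 | 3.0–3.9 | Large (6–8) | Moderate (4–6) | 3 or 2 | 10 |

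Total 10 + 20 + 10 = 40 conflicting pairs. All other finals from baselines 8 and 6 agree in both rows. There is no overlap at 4, and no pair is left unclassified at one decimal. Assigning 8 and 6 to one row each removes all 40 conflicts.

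**Result 2: targets not lowered.** All 29 unchanged targets from 0.1 to 2.9 return Moderate; 2.5→2.5 is category 2 with a reduction of (2.5 − 2.5)/2.5 = 0%. A target raised but still below 3, such as 2.0→2.5, is also Moderate. Unchanged targets of 3 or more are Minimal in every row that applies.

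**Set against Table 1.** Strategy 2 reduces the calcineurin inhibitor first, to "target trough concentrations of tacrolimus of 3–5 ng/mL". From a baseline of 6, every value in that range is in conflict: 3.0–3.9 is Large or Moderate, and 4.0–5.0 is Moderate or Minimal. From a baseline of 8 the same range is not in conflict, because only finals of 6.0–6.9 are.

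**When the conflict reaches the outcome.** A participant in category 4 or 5 is unaffected. Otherwise the largest class over all non-steroid drugs applies:

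- another drug at Moderate: 8→6.0–6.9 and 6→4.0–5.9 resolve to Moderate; 6→3.0–3.9 stays open;
- another drug at Large, or a qualifying conversion: all three resolve to Large.

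In Table 1's Strategy 1 the antimetabolite is first cut by at least 50% (Moderate or Large in Table 3) and then stopped (Large) before the calcineurin inhibitor is lowered. A participant who follows that sequence is graded Large whichever tacrolimus row is used. Under Strategy 2, a participant who responds to the calcineurin inhibitor step alone has nothing else to settle the class.

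**The case against.** The strongest reply is that this is a notation slip with narrow reach. The ≥8 row plainly includes 8, and the <4 row leaves 4 to the row above it, so both clear edges include the lower bound; by the same convention 6 belongs to 6–8. The category 4 and 5 events and the largest-reduction rule remove many conflicts. On unchanged targets, the text speaks of a reduction, and a participant with none belongs in category 1 whatever a table cell says. Baselines below 3 may also be uncommon, given that Table 1 aims at 3–5 or 5 ng/mL.

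The narrowing stands. The convention is a sensible inference, but it is not written, and the printed 6–8 and 4–6 rows contradict it. The largest-reduction rule ranks drugs, not rows for one drug, so it is not a stated tie-breaker. If the text overrides the <4 row, then text and table disagree and one must be corrected.

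Several stronger readings are tempting and should not be drawn:

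- **A count of affected participants.** Assuming 10–20% have a baseline of exactly 6 or 8 would give 28–56 of 280. The article gives no such share, and the product leaves out the other conditions above.
- **Unblinded staff choosing the row.** The article says treating clinicians specify targets. It does not say who derives the class, and an Endpoint Verification Committee is planned.
- **Measured troughs as the baseline.** The column is headed Baseline trough, but the text settles that targets are compared.
- **Gaps between cells.** Cells such as 4–5.9 and ≥6 leave no gap at one decimal, and nothing suggests finer recording.

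**Conclusion.** The scoring rule for categories 1 to 3 is wrong as printed in two respects: it is double-valued at baseline targets of 8 and 6 for the finals listed, and it grades some unchanged or raised targets below 3 as Moderate. Each error is worth one level of the outcome, and only for participants who are not in category 4 or 5 and whose class is not fixed by another drug change or conversion. How many that is cannot be derived from the article, because it gives no distribution of baseline targets. Whole-number targets are plausible since clinicians specify them, but that is an assumption, as is the rarity of baselines below 3.

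The full protocol or analysis plan may hold a tie rule. The point still stands against the article, which prints the conflicting rows rather than leaving them out. It is evidence of an endpoint definition to be corrected, not of bias in favour of either arm.

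**What to change.** For outcome scoring only:

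1. Make the tacrolimus baseline rows mutually exclusive, for example ≥8; ≥6 to <8; ≥4 to <6; <4, which follows the lower-bound-inclusive pattern of the ≥8 and <4 rows. The row chosen for 6 and 8 determines the class in all 40 conflicting pairs, so it should be stated explicitly.
2. State that a final target not lower than the baseline target is Minimal, before the table is applied.
3. Derive the class by program from the recorded targets, and rescore any participants already entered before the next analysis that uses this outcome.

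Heading the column Baseline target trough is an optional editorial alignment with the text.

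The cost is a corrected table and a short derivation program. Both targets are already to be collected, so no new data are needed, and no treatment target changes.
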